#### Clinician nudge to order

For the “Order” clinician nudge, the Epic SmartSet function also will be utilized. The SmartSet will include 1) genetic testing order with a default set of condition-specific genes and a testing lab selected; 2) Epic Smartphrase to populate the clinician’s note regarding the discussion and plan for genetic testing; and 3) Epic Smartphrase to populate the patient’s after visit summary with information about genetic testing. The list of genes included in the testing is based on guidelines and condition expert recommendation. The selection of the testing laboratory also will be sensitive to the patient’s insurance, so if the patient is capitated to a certain commercial testing laboratory that offers appropriate testing, the testing will go to that laboratory. Genetic testing information text for patients was developed with input from study partners and approved by the legal team (Supplemental Figure 2). The one-page text contains language about the possibility of different types of genetic test results (positive, negative, variant of uncertain significance), implications for family members, guidance on how to learn more about test cost and lab billing policies, and other insurance implications including the Genetic Information Non-discrimination Act (GINA) [90, 91]

The clinician nudges also contain a link for an informational website, designed to provide clinician-facing information about genetic testing, processes to place referrals to genetics, order genetic testing, results management, and frequently asked questions. Screenshots of the nudges, Epic SmartSets, and the homepage of the provider informational website are included in Fig. 3.

#### Nudge to patient and clinician (refer or order)

The arms with patient and clinician nudges encompassing the steps outlined above.

#### Procedures and measures

To launch the nudges, a multi-phase approach will be used. EHR phenotyping algorithms will first be tested by conducting chart reviews. Initially, 20 charts will be reviewed to confirm a patient identified by the algorithm has the targeted diagnosis. Next, 100 charts will be reviewed, and the algorithm will be refined until achieving at least 85% accuracy. This process is iterative until an 85% positive predictive value is reached. In the next phase, a clinician alert will fire invisibly in the background of the EHR without prompting nudges to patients or clinicians. The results of these background alerts will be evaluated to verify accuracy and adjust the EHR algorithm as needed. Subsequently, the clinician nudges will be activated for several weeks among a limited number of clinicians. We will compare the patients identified through the algorithm and confirm that those patients and clinicians who should have received nudges are receiving them. We will also solicit feedback from clinicians on the acceptability of the alerts. Nudge delivery will be monitored in all arms throughout the trial.

The primary measure of implementation is time to genetic testing. The clock begins running with the first (index) visit to a randomized clinician, and ends with either a testing event, or censorship at six months. Those patients who may have multiple visits and cross from a clinician randomized in one group (order nudge, refer nudge or no nudge) to a clinician randomized to a different group will be censored out of the primary analysis at the time of crossover. However, observation will continue out to the end of six months, and a secondary analysis may include those exposures to different clinician arms. Secondary measures of implementation will be the time to genetics referrals and genetic test orders, defined as referrals to genetics placed, and orders for genetic testing, completed or not. Patient engagement rate will be assessed by the frequency of patient responses to text messages, as well as views of the genetic testing informational video. Patient information (e.g., sex, race, condition) will be ascertained from the EHR.

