**Fig. 2 Fig2:**
[figure not shown]
Patient Nudges. **a** Text message language. **b** Still image from the patient animated explainer video

Primary and secondary implementation outcomes, and contextual factors that shape implementation effectiveness (e.g., clinician location, patient demographics) will be captured. Prior to the nudges being sent out, electronic phenotyping algorithms will be used to identify patients for whom genetic testing is recommended based on published guidelines and expert opinion [2, 3, 7, 10]. Conditions were selected for which 1) genetic testing is considered standard of care due to implications for medical management; 2) the genetic testing approach is standardized; and 3) effective electronic phenotyping with a positive predictive value (PPV) [39, 86] of over 85% can be performed (Supplemental Table 1). With a lens of health equity, preliminary data also were collected for these medical conditions highlighting existing disparities in genetic testing rates by race.

Once identified through electronic phenotyping, patients are randomized to patient nudge or no nudge. Patients who already have had genetic testing for the condition of interest will be excluded. Depending on randomization group, clinicians will receive a nudge in the form of an alert prompting them to “Refer”, or place a referral to the appropriate genetics clinic, or “Order” action, meaning order genetic testing themselves, as viewed in Fig. 3. Randomization of clinicians was done by first grouping clinicians who work together into clusters using the “group_id” network analysis routine in Stata 18. Clusters were then randomly assigned without replacement to one of the two clinician nudge arms or to usual care (no nudge). The alerts will activate at the time of the patient visit when the clinician opens the patient’s EHR. These alerts are static and on the ‘storyboard’ component of the chart, so the provider can view the alert throughout the visit, independent of the tab that is open (Fig. 3). The alerts may transition to interruptive (pop-up) alerts should there be a lack of engagement during the pilot phase of the study.

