**Fig. 3 Fig3:**
[figure not shown]

[figure not shown]
Clinician Nudge. **a** Clinician alert. **b** Clinician Order nudge. **c** Clinician Order SmartSet. **d** Clinician Refer nudge. **e** Clinician Refer SmartSet. **f** Clinician education website homepage. Publicly available link: https://www.med.upenn.edu/agm/

Patients, depending on randomization arm, will receive a nudge to discuss genetic testing with their clinician through the Penn Way to Health program, an evidence-based patient engagement platform used in ongoing studies [87, 88]. Patients will receive a text message around one week prior to their appointment, as well as around three days prior to the appointment (Fig. 4).

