#### Patient selection

Patients will be selected by using the following parameters: 1) patient has a condition included in the trial and is identified through an electronic phenotyping algorithm (Supplemental Table 1); 2) patient is over the age of 18 years old; 3) patient has been seen for two encounters with the condition within the last three years; and 4) patient is seeing a clinician identified for randomization. The details of electronic phenotyping algorithms used for this project, which include ICD-10 codes, laboratory measurements, and medication data, will be published separately. Electronic phenotyping methods were validated using manual chart review of sets of randomly selected patient charts to ensure correct identification of patients eligible for the trial. A positive predictive value of at least 85% is required before finalizing any phenotyping algorithm. The EHR algorithms also exclude patients who have previously received genetic testing.

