### Patient nudges and support

The patient nudge is designed to “prime” the patient to discuss the potential benefits of genetic testing with their clinician at the time of their next appointment. The patient nudge will be delivered via text message directly to the patient’s cell phone through the Penn Way to Health program. Text messaging was selected as the mode of nudge delivery since an estimated 25% of patients do not use the patient portal as a conduit for health information. National survey data identified that compared to White individuals, Black and Hispanic individuals were less likely to be offered patient portal access and among those offered, were also less likely to access their portal [89]. If sent, the patient nudge will be delivered around one week prior to their medical appointment, and then again around three days prior to their appointment. Additionally, the patient nudge will contain a link to a two-minute informational video providing basic background on genetic testing created as part of this trial (Fig. 4).

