#### Sample size, power, and statistical analysis

Based on preliminary data, up to 3800 patients are anticipated to be available to include in the study (based on prior assessment of eligible patients over the past three years), interacting with approximately 230 clinicians represented by approximately 100 clinician clusters. Clinician nudge assignment will be randomized by clinician cluster, while patient nudges will be assigned independently. This independent randomization makes the main effect for patient nudges a within-cluster comparison. The analysis will use the time to genetic testing outcome registered in the EHR within six months after the visit when the nudges were delivered. The exchangeable correlation (for our clustered data) observed from other studies is small (0.07). Our goal is to achieve at least 80% power using a two-sided type-1 error of 5%. Based on prior data, our outcome is expected to be 10% in the absence of intervention by the 6-month censoring time. We anticipate that the patient nudge will increase testing by 5% (HR=1.54), and clinician nudges will increase testing by 10% (HR=2.12). In addition, the two nudges together may increase testing more than the strict additive main effects and add up to an additional 10% testing (25% total increase). We calculated power by simulating random data sets in Stata 18. We assumed an exponential daily hazard with event times correlated within cluster and fitted those data sets with aCox regression model. Model variances were corrected using cluster-correlation. Our design yields more than 95% power for the patient and provider nudges regardless of correlation. It also provides at least 90% power to detect (within-between) interactions. Power remains above 80% for a wide variety of departures from our original assumptions. Power for the main effect of provider nudges may drop below 80% for high within-subject correlations (above 0.2), and overall power to detect all differences is reduced as the baseline hazard increases (beyond 20% testing by 6 months).

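### The primary clock starts at the attended index visit, after patients have been randomised and texted, so the patient-nudge contrast is conditioned on attendance that the text may change.

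*Protocol article*

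**What the plan says.** The order of events is fixed in several sections of the Protocol article.

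- **Randomisation** (Study design): "Once identified through electronic phenotyping, patients are randomized to patient nudge or no nudge".
- **Texts** (Study design; Patient nudges and support): "Patients will receive a text message around one week prior to their appointment, as well as around three days prior to the appointment". Their purpose is to prompt the patient "to discuss the potential benefits of genetic testing with their clinician at the time of their next appointment".
- **Time zero** (Procedures and measures): "The clock begins running with the first (index) visit to a randomized clinician". Follow-up "ends with either a testing event, or censorship at six months". Study design agrees, counting six months from the initial visit with a randomised clinician.
- **Another wording** (Sample size, power, and statistical analysis): the outcome is testing "within six months after the visit when the nudges were delivered".
- **Prior testing** (Patient selection): "The EHR algorithms also exclude patients who have previously received genetic testing". The exclusion sits in the identification algorithm.
- **Clinician alert** (Study design): it fires when the clinician opens the chart at the visit.

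The article does not say how a randomised patient who never attends is handled.

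**The concern.** The whole patient intervention is delivered before time zero. A patient enters the Cox risk set only by attending, and the text is about that very appointment, so it could plausibly raise or lower attendance. If it does, attenders in the two arms are no longer exchangeable, although the patients randomised were.

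The patient nudge is the one factor that is randomised individually and compared within cluster. Conditioning on an event after exposure gives up part of that protection, and more patients do not restore it. It also leaves out any gain in uptake that the text achieves by bringing more patients to the visit.

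**Working it through.** **Inputs from the Protocol article** (Sample size, power, and statistical analysis): 10% tested by six months without intervention; patient nudge +5 points, HR 1.54; clinician nudge +10 points, HR 2.12; up to 3,800 patients; two-sided 5% alpha; more than 95% power claimed.

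**Assumed, because the documents do not give them:** 1:1 patient allocation (1,900 per arm); control attendance *a* of 75 to 90%; a change *d* in attendance caused by the text; testing risk *q* of 0 to 30% in the extra attenders.

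**1. The plan's own figures.** With an exponential hazard, HR = ln(1 − p1)/ln(1 − p0).
- Patient nudge: ln(0.85)/ln(0.90) = 1.54.
- Clinician nudge: ln(0.80)/ln(0.90) = 2.12.

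Both match. With equal cells and additive risks, the average over clinician arms is (10 + 20 + 20)/3 = 16.7% without and 21.7% with the patient nudge. A two-proportion test at 1,900 per arm then has 97.5% power, and an event-based calculation gives above 99.9%. The claim of more than 95% stands for the patient nudge.

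**2. Attendance changes, no effect on testing once seen.** Those who would attend anyway test at 10% in both arms.
- From the visit: p1 = (0.10*a* + *dq*)/(*a* + *d*), compared with p0 = 0.10.
- Per randomised patient: 0.10*a* + *dq*, compared with 0.10*a*.

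| *a* to *a* + *d* | *q* | p1 from the visit | HR from the visit | Per randomised | HR per randomised |
|---|---|---|---|---|---|
| 75% to 80% | 0% | 9.4% | 0.93 | 7.5% vs 7.5% | 1.00 |
| 75% to 80% | 30% | 11.25% | 1.13 | 7.5% vs 9.0% | 1.21 |
| 80% to 85% | 0% | 9.4% | 0.94 | 8.0% vs 8.0% | 1.00 |
| 80% to 85% | 5% | 9.7% | 0.97 | 8.0% vs 8.25% | 1.03 |
| 80% to 85% | 30% | 11.2% | 1.12 | 8.0% vs 9.5% | 1.20 |

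Over *a* = 75 to 90% and *d* = 2 to 5 points, the HR from the visit stays between 0.93 and 1.13. The fourth row shows that the two clocks can disagree in sign: more patients are tested overall, yet the visit clock shows fewer.

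**3. Testing between first text and visit.** The control daily hazard is −ln(0.90)/182.5 = 0.000577. Over seven days:
- control: 1 − exp(−7 × 0.000577) = 0.40%, about 8 of 1,900;
- HR 1.54: 0.62%, about 12 of 1,900.

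The difference is 0.22 points. If 5% of the nudged arm's tests came before the visit and were lost, with none lost among controls, p1 would be 0.1425/0.9925 = 14.4% and the HR 1.47 instead of 1.54.

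**4. Cost of counting all randomised patients.** Take the planned 10% vs 15% in attenders, with non-attenders untested.
- 80% attendance in both arms: 8.0% vs 12.0%, HR ln(0.88)/ln(0.92) = 1.53, power about 98%.
- 80% vs 77%: 8.0% vs 11.55%, HR 1.47, power about 96%.
- 80% vs 85%: 8.0% vs 12.75%, HR 1.64.

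These use the no-clinician-nudge rates throughout. Averaged over clinician arms at 80% attendance, the rates are 0.8 × 16.7 = 13.3% and 0.8 × 21.7 = 17.3%, with about 93% power. Either way, power stays well above the 80% goal.

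**The case against.** The visit is a sensible origin for half of this factorial design. The clinician alert exists only once the chart is opened, clinician effects are tested before patient effects, and one Cox model carries both. Moving the origin for the whole model would add unexposed time and patients who cannot be exposed to the clinician comparison. That stands, and it is why the change should be confined to the patient-nudge contrast.

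The entry rule is also the same in both arms: controls must attend too. Bias arises only if the text changes attendance, on which the documents have no data. That stands as a limit on size. How never-attenders are handled could be set out in a fuller document, but the article does fix the clock, and under that clock they have no start date.

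Stronger readings that a reader might infer are not supported:
- *Patients who reschedule are lost.* The clock starts at the first visit whenever it takes place, so they enter then.
- *An order placed before the visit removes the patient.* The primary event is testing; orders are a secondary measure.
- *Patients tested between text and visit are excluded as already tested.* The exclusion belongs to identification; nothing says it is reapplied at the visit. Step 3 shows that this route is small in any case.
- *There is a rival time zero.* The phrase about the visit when nudges were delivered reads as loose shorthand for the index visit. It fits the clinician alert but not the texts, and has no literal meaning where no nudge is sent. It needs rewording only.

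**Conclusion.** The point holds for the patient-nudge and combined arms. By the article's stated rule, the individually randomised contrast is restricted to attenders after exposure. It is a problem of validity and of what is being estimated, not of power.

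The size is probably modest: HR 0.93 to 1.13 in place of 1.00, against a planned 1.54. That range rests on assumed attendance and on wide assumed testing risks in the extra attenders, and the direction cannot be predicted. It would be too strong to say that the randomisation as a whole is undone: the clinician-only nudge is delivered at the visit and is not affected, and if the text leaves attendance unchanged the patient contrast is sound. The correction is worth making because it is cheap and removes the dependence on that unknown.

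**What to change.** For the patient-nudge contrast:
- Start the clock in both arms on the date the first text was or would have been sent for the first eligible appointment, or on the scheduled date of that appointment.
- Fix eligibility and untested status on that date.
- Analyse every randomised patient from that date, whether or not the visit takes place, with non-attenders kept at risk.
- Report attendance and testing before the visit by patient arm.

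Keep the index-visit origin for the clinician-nudge contrast, and as a supportive analysis for the patient nudge. Reword the phrase in Sample size, power, and statistical analysis so that it agrees with Study design and Procedures and measures.

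The cost is one additional model with its own origin and a date that should be derivable from scheduling data, since the texts are timed from the appointment. Missed visits dilute the absolute patient-nudge effect from 5 to about 4 points at an assumed 80% attendance, while the HR moves only from 1.54 to 1.53.

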#### Sample size, power, and statistical analysis

Based on preliminary data, up to 3800 patients are anticipated to be available to include in the study (based on prior assessment of eligible patients over the past three years), interacting with approximately 230 clinicians represented by approximately 100 clinician clusters. Clinician nudge assignment will be randomized by clinician cluster, while patient nudges will be assigned independently. This independent randomization makes the main effect for patient nudges a within-cluster comparison. The analysis will use the time to genetic testing outcome registered in the EHR within six months after the visit when the nudges were delivered. The exchangeable correlation (for our clustered data) observed from other studies is small (0.07). Our goal is to achieve at least 80% power using a two-sided type-1 error of 5%. Based on prior data, our outcome is expected to be 10% in the absence of intervention by the 6-month censoring time. We anticipate that the patient nudge will increase testing by 5% (HR=1.54), and clinician nudges will increase testing by 10% (HR=2.12). In addition, the two nudges together may increase testing more than the strict additive main effects and add up to an additional 10% testing (25% total increase). We calculated power by simulating random data sets in Stata 18. We assumed an exponential daily hazard with event times correlated within cluster and fitted those data sets with aCox regression model. Model variances were corrected using cluster-correlation. Our design yields more than 95% power for the patient and provider nudges regardless of correlation. It also provides at least 90% power to detect (within-between) interactions. Power remains above 80% for a wide variety of departures from our original assumptions. Power for the main effect of provider nudges may drop below 80% for high within-subject correlations (above 0.2), and overall power to detect all differences is reduced as the baseline hazard increases (beyond 20% testing by 6 months).

Time to event outcomes (incidence of testing, incidence of ordering, incidence of referring, incidence of clinician action) will be analyzed using Cox regression, censoring at the six-month end of observation. The study design is factorial, and models will contain categorical predictor terms for clinician (refer vs. order vs. control) and/or patient nudge vs. control. We will include adjustments for fixed effects of site. We will control for type 1 error inflation by hierarchical testing, starting with the overall model significance, followed by overall effects of clinician nudges and then patient nudges. Once we have fitted the main effects model, we will test for interaction between clinician and patient nudges and retain that interaction term if significant (alpha=5%). We will test the two clinician nudges separately and combine them if there are no significant differences, and use a similar approach for other study outcomes using GLM (or GEE for repeated measures) using the appropriate distribution family.

While our design is factorial, with the presumption that a patient will remain in one clinician cluster, we recognize that there will be some movement or crossover between clinician clusters and treatments. For that reason, our primary analysis will censor patient observations at the point of crossover. We will also conduct a secondary analysis “as treated”, using time-varying covariates to represent the accumulated clinician nudge exposures over time.

Next, we will examine variability in our outcomes by treatment arm and moderators (patient-, clinician-, and system-level) using interaction terms within the regression. We will fit an adjusted model using the same approach described in the primary analysis. Moderators of particular interest will be patient-level (e.g., diagnosis, race, geocoded indicator of socio-economic status), clinician-level (e.g., years in practice), and system-level data (e.g., community vs. hospital-based). If there are no interactions with the two clinician nudge arms, they will be combined in subsequent moderator analysis following the same approach described above.

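### The stated power of at least 90% for the clinician-by-patient interaction does not follow from the printed effects; in the planned Cox model it is about 24%

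*Protocol article*

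**What the plan says.** Everything is in the protocol article, section 'Sample size, power, and statistical analysis'.

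- Baseline: "our outcome is expected to be 10% in the absence of intervention by the 6-month censoring time".
- Single nudges: "the patient nudge will increase testing by 5% (HR=1.54), and clinician nudges will increase testing by 10% (HR=2.12".
- Both nudges: together they may raise testing "more than the strict additive main effects and add up to an additional 10% testing (25% total increase"). The four cells are therefore 10%, 15%, 20% and at most 35%.
- Size: "up to 3800 patients are anticipated to be available to include in the study", with "approximately 230 clinicians represented by approximately 100 clinician clusters".
- Target: "Our goal is to achieve at least 80% power using a two-sided type-1 error of 5"%.
- Power was simulated with exponential event times correlated within cluster, fitted by Cox regression with cluster-corrected variances. The result for the interaction: "It also provides at least 90% power to detect (within-between) interactions".
- Planned test, after the main-effects Cox model: "we will test for interaction between clinician and patient nudges and retain that interaction term if significant (alpha=5"%).

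**The concern.** The extra benefit of nudging both parties is described as an excess over the sum of two percentage-point gains. The test that is meant to detect it asks a different question: whether the combined hazard ratio exceeds the product of the two single hazard ratios. When both single effects are positive, the product already predicts more than the sum, so part of an additive excess is not an interaction on the Cox scale. The power for that test must be worked out for what is left.

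The stake is interpretation. A reader told that power was at least 90% would take a non-significant interaction as good evidence that the two nudges do not reinforce each other. If power is nearer one in four, a non-significant result is what to expect even when the full assumed excess is real.

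**Working it through.** **Inputs from the article.** Cell risks 10/15/20/35%; 3,800 patients (the power section gives this as a ceiling, the 'Duration' section as a minimum); about 100 clusters, so about 38 patients each; correlation 0.07; two-sided alpha 5%; exponential hazard; censoring at six months.

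**Assumptions.** The allocation ratios are not printed. I take 1:1:1 for the clinician arms and 1:1 for the patient nudge, and vary this below. No loss to crossover censoring is applied.

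**Step 1: reproduce the printed hazard ratios.** Under an exponential hazard, HR(p) = ln(1 − p) / ln(1 − 0.10).

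- 15%: ln 0.85 / ln 0.90 = 1.54, as printed.
- 20%: ln 0.80 / ln 0.90 = 2.12, as printed.
- 35%: ln 0.65 / ln 0.90 = 4.09 (not printed).

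**Step 2: interaction on the Cox scale.**

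- No interaction predicts 1.5425 × 2.1179 = 3.27, a six-month risk of 1 − 0.90^3.27 = 29.1%.
- Interaction HR = 4.0887 / 3.2669 = 1.25; its log is 0.224.

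**Step 3: power.** With the clinician arms pooled, the cells hold 633, 633, 1,267 and 1,267 patients and expect about 63, 95, 253 and 443 events.

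- SE = √(1/63.3 + 1/95 + 1/253.3 + 1/443.3) = 0.180.
- z = 0.224 / 0.180 = 1.24; power = Φ(1.24 − 1.96), about 24%.

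**Step 4: sensitivity.**

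| Setting | Interaction HR | Cox power |
|---|---|---|
| Clinician arms pooled, both = 35% | 1.25 | 23.8% |
| One clinician arm vs control | 1.25 | 20.7% |
| Equal 2 × 2 split | 1.25 | 28.7% |
| Pooled, both = 30% | 1.04 | 5.4% |
| Pooled, both = 39.1% (10 points above the multiplicative prediction) | 1.44 | 53% |
| Pooled, both = 50% | 2.01 | 97.5% |

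Simulation on the plan's model (100 clusters of 38, exponential times, cluster-robust Cox, 500 runs per setting) gives 28%, 25% and 25% at correlations 0, 0.07 and 0.2. Clustering is therefore not the cause. With refer and order kept apart (2 df), the same runs give 22%, 18% and 22%.

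**Step 5: what 90% would need.** The interaction HR must reach exp((1.96 + 1.2816) × 0.180) = 1.79, about 46% testing in the combined cell. At HR 1.25 it would take about 25,800 patients.

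**Step 6: the same excess as a risk difference.** The contrast is 35 − 20 − 15 + 10 = 10 points.

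- Arms pooled: SE = √(0.09/633 + 0.1275/633 + 0.16/1,267 + 0.2275/1,267) = 0.0255; z = 3.92; power 97%.
- One clinician arm vs control: SE = √((0.09 + 0.1275 + 0.16 + 0.2275)/633) = 0.0309; z = 3.24; power 90%.
- With a 5-point excess (both = 30%): about 51% pooled. For one arm, SE = √(0.5875/633) = 0.0305, z = 1.64, power about 37%.

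These risk-difference figures make no allowance for clustering.

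**Main effects.** A Schoenfeld calculation at the printed hazard ratios gives more than 99% for both nudges, so the article's main-effect claims reproduce.

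**The case against.** Much of the case on the other side stands, and it limits what follows from the arithmetic.

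- **The simulated interaction is not printed.** The article does not say which interaction size lay behind the 90%, so its origin cannot be determined. A reader might infer that the authors confused the two scales. The 90% would suit a risk-difference test, but that is inference. What can be said is that the printed effects and the planned model do not produce it. Any larger effect that would produce it conflicts with the 25-point total increase.
- **The fallback model does little harm.** A reader might infer that dropping a non-significant interaction leaves a model that overstates each nudge and hides the synergy. The figures do not support this. Fitted to the expected cells, the main-effects model gives hazard ratios of 1.85 and 2.44 but six-month risks of 9.0, 16.0, 20.5 and 34.6%, each within about one point of 10, 15, 20 and 35%. Those hazard ratios are averages over the other factor: the patient effect is 1.54 without and 4.09 / 2.12 = 1.93 with a clinician nudge. The 'Study design' section also plans to analyse each of the six groups separately.
- **The Cox scale is legitimate.** Interaction on the hazard scale is a reasonable choice for a time-to-event outcome. Exactly additive effects (25% with both) would give an interaction HR of 0.84, but that is ordinary scale dependence, not an error.
- **Nothing primary moves.** The testing hierarchy runs from the overall model to clinician and then patient nudges. The sample size is the number of patients available.

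None of this restores the 90%.

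**Conclusion.** The interaction power statement is wrong as written. On the article's own effects, model and sample size, Cox interaction power is about 24%, or 21–29% over the allocations tried, against a stated minimum of 90%. Since the excess is given as a maximum, 35% in the combined cell is the favourable case; at 30% power is about 5%. Crossover censoring, which is planned but not allowed for here, would lower these figures.

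The result rests on the exponential hazard stated in the article and on assumed allocation ratios, and it is not sensitive to the within-cluster correlation up to 0.2. It is confined to the interaction: main-effect power, error control and enrolment are unaffected. The practical consequence is that a non-significant Cox interaction, expected in about three of four such trials under the plan's best case, says little about whether the two nudges together do more than their sum.

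**What to change.** 1. Restate the Cox interaction power as about 25% for an interaction HR of 1.25, or state the interaction HR for which 90% holds (about 1.8, some 46% testing with both nudges). If the simulation used another interaction size, print it and reconcile it with the 25-point total increase.
2. Beside the Cox term, not in its place, add a six-month risk-difference interaction contrast with cluster-robust variance, for example from Kaplan–Meier risks or an identity-link model. State its power as about 90% (one clinician arm vs control) to 97% (arms pooled) at the full 10-point excess, and about 37–51% at a 5-point excess.
3. Say in advance that a non-significant Cox interaction will not be taken as evidence against a more-than-additive benefit.

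The cost is a change of wording and one further contrast on data already collected. No extra patients are needed, though the published interaction power becomes much less favourable.
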